### Data analysis

Data analysis aims to determine the outcome of each phase of this study. For Phase 1 (Qualitative study), all data from FGD recordings will be transcribed verbatim and managed by using NVivo 12 software. The content analysis will start with the data encoding form of the verbatim transcripts from the FGDs (3 units of analysis) and in-depth interviews (12 units of analysis). We will read each transcript several times to determine the coding. Then, the codes that have the same meaning will be grouped into categories, which are then grouped into themes. The researchers will integrate each theme into a qualitative description. Codes and themes will be agreed upon by the researcher teams [31].

For Phase 2 (Qualitative study) in the HE method, data analysis at this phase will be done by grouping the problems found by the experts according to the HE principle. The list of problems that have been identified and agreed upon by the experts is given an assessment of the severity of the problem and calculated as the absolute severity of each problem and reported according to the severity rating table in Table 1 [23].

**Table 1 pone.0277127.t001:** Severity rating.

Scale	Term	Description
0	No problem	Not a usability problem.
1	Cosmetic problem	The problem is only on the display side, it has no effect on user comfort.
2	Minor Problem	Problems need improvement but with little priority.
3	Major Problem	Problems need high priority fix.
4	Catastrophe	The problems received by users are very large, complex and harm the users, improvements must be made.

In the TA method, the problems found can arise from the comments and behaviour of the participants recorded when using the IDSM Application. The audio recording data will be transcribed verbatim by the researchers and cross-checked for accuracy of representation among the researcher team. The results of the transcript will be analysed to find problems in the operation of the application software carried out by users. The results of this analysis will be in the form of a group of problems found in the operation of the application software. The data will be processed using descriptive statistics. Furthermore, a rating will be given to each assessment parameter that is analysed [32].

## Security and data management plans

All data collected during the study will be kept confidential and all researcher team members will be bound by data confidentiality. The data collected from all phases will be anonymized and stored securely in a computer database. Quantitative data will be anonymized for statistical analysis. The analysis of all qualitative data will be conducted anonymously in pseudonymous form (i.e., without the name of the person, institution or location). The recorded data will be deleted after the study is completed if there is a request from the participants. For reporting the results of the qualitative study, the Consolidated Criteria for Reporting Qualitative Research (COREQ) checklist will be used [34]. Reporting the results of the quantitative study will use the Transparent Reporting of Evaluations with Nonrandomized Designs (TREND) checklist [35]. This study will provide opportunities for other researchers who need those data by contacting the corresponding author. Dissemination of findings and data sharing will be done after this research is completed. The data will be provided as part of the manuscript. Once we finished with data collection.

## Expected results

Phase 1 (Qualitative study). The outcome of this study will be described through the themes found which will later be used as the content of the application software that will be developed. Phase 2 (Qualitative study). Based on the results of phase 1 and the literature review, we will develop an android-based IDSM Application that has been usability tested and can be readily applied. Phase 3 (Quantitative study), the main outcomes expected in this phase are the android-based IDSM Application that effectively improves self-management and glycemic control of Patients with T2DM.

## Ethical considerations

We will use an information sheet and a consent form as prove that all participants are well informed and agree to participate. All participants will be given the information verbally in addition to written information in detail about the purpose, benefits and possible side effects, confidentiality of information, freedom to refuse and can resign at any time during the study. For participants who cannot read or write, an explanation about the research and informed consent will be read for them by researcher and then participants are asked to give a thumbprint as proof of their willingness to take part in the study. Patients who can’t buy or will not have smartphone will be given a module after research finish. Each participant has the right to refuse or discontinue participation at any time before or during data collection, without giving reasons. Ethical approval for conducting this research was obtained from the Medical and Health Research Ethics Committee of the Faculty of Medicine, Public Health and Nursing Universitas Gadjah Mada with the number of: KE/FK/1068/EC/2021 on September 27, 2021.

## Timeline of the study

The estimated time for this study is ten months which is divided into three phases. Phase 1 will be conducted for three months, phase 2 will be conducted for four months and phase 3 about three months.

### Study risks

The risk that may occur in this study is that not all Patients with T2DM who are members of PROLANIS in Yogyakarta city use android-based applications in carrying out their self-management, so it is possible that many patients still cannot operate the applications. To anticipate these problems, researchers will provide training on how to use the IDSM application and will provide assistance until participants can operate the application software. In addition, to anticipate errors in entering self-managed data for three months, the researchers will monitor every day through the data server and provide reminders to the participants.

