### Study aims

The main aim of this study is to determine the effectiveness of an android-based IDSM application in self-management and glycemic control of patients with T2DM. The study’s specific aims are: 1) to explore perceptions about understanding, skills, barriers and needs of patients with T2DM, their families and nurses in using android applications to carry out diabetes self-management; 2) to develop an android-based IDSM application that can be used by patients with T2DM, their families and nurses; and 3) to determine the effectiveness of the application in self-management and glycemic control of patients with T2DM.

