Phase 3 (Quantitative study). This phase will use a non-equivalent control group design, which applies a pre-repeated post test control group design. Participants in this phase are Patients with T2DM, family caregivers, and nurses according to the inclusion criteria. The experiment and control group are determined by the person in charge of PROLANIS at PHC based on geographic location and PROLANIS activity evaluation data. Data collection will be conducted at two PHCs which has the lowest patients with T2DM number of visits based on data from BPJS Health. However, if the number is not sufficient, it will expand to other PHC. The experiment group will be given IDSM Application, and the control group will use the whatsapp group to communicate or consult directly with a health provider. Self-management will be carried out independently by the patient in his or her home. Monitoring by a health provider will be carried out using whatsapp group and when patient come to the PHC for routine check up. Determination of research subjects will be done by consecutive sampling on patients with T2DM. The sample size was calculated based on the formula for calculating sample size from Lemeshow by considering the hypothesis test for two populations means “two sided” test, with α = 5%; Z(1-α) = 1.96; β = 20%; Z(1-β) = 0,84, standard deviation = 0,9 with mean difference = 0.6 [26], then the calculation of the sample size is obtained n1 = n2 = 35 participants. To anticipate the possibility of participants dropping out, a number of samples will be added to keep them fulfilled by the formula: n’ = n/(1-f) [27]. As a result, four participants will be added so the number of samples needed is n1 = n2 = 39 participants. The sample will be divided into two groups, each group consisting of 39 patients with T2DM included in the experiment group and 39 Patients with T2DM included in the control group. The sample will be selected according to the inclusion criteria.

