After participants are given an explanation beforehand, they will complete an informed consent forms, then they will provide sociodemographic data including religion, marital status, latest education, occupation, and income. The experiment group will first install the app, they will also get IDSM e-module and training how to use the apps before they actually using it. Meanwhile, the control group will only get e-modules. Measurement of diabetes self-management and HbA1C will be conducted before and after the intervention. The Indonesian Version- Diabetes Self-Management Instrument (IDN-DSMI 35) will be used to measure self-management of patients with T2DM. This instrument is valid and reliable with Cronbach’s Alpha values of 0.96 and 0.84–0.93 for the subscales. IDN-DSMI can measure self-management behaviour among Indonesian patients with T2DM at PHC [28]. Measurement of self-management scores will be done once a month for three months after the intervention both in the experiment group and in the control group. Based on Lally Gardner (2013), it takes 21 days to form a habit in changing behaviour [29]. The measurement of HbA1C will be conducted before and in the third month after the intervention both in the experiment group and in the control group. Two research assistants will be involved in measuring the self-management score of patients with T2DM. They will previously be given training to ensure the same understanding and perceptions among the to measure self-management and HbA1C. Kappa testing will be conducted to measure inter-rater reliability. The research assistants involved will be persons with minimum education of a bachelor’s degree in nursing. The flow of data collection in phase 3 is shown in the following Fig 2.

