### Strengths and limitation

This study offers availability of an integrated diabetes self-management program using Indonesia-language. An android application that involves patients, families and nurses and is useful to guide patients and facilitate monitoring of families and nurses to pay more attention to the implementation of the self-management of patients with diabetes in order to improve their self-management and glycemic control. This android-based IDSM Application can also be used as a means to evaluate the implementation of PROLANIS program at the PHC level, especially among Patients with T2DM.

One limitation in this study is that this research specially in phase 3 will be conducted in three months which might have the potential of participants to drop out before the study is finish. To anticipate this, researchers will monitor and evaluate every day through the server and conduct self-management measurements once a month.

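### Daily researcher monitoring and reminders very probably reach app users only, so the between-group difference may include a researcher follow-up effect that the plan would credit to the app

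*Protocol article*

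**What the plan says.** Study risks describes the follow-up. To head off errors when patients enter their self-management data over three months, "the researchers will monitor every day through the data server and provide reminders to the participants". The same paragraph deals with patients who cannot operate the app and promises them training and assistance.

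Strengths and limitation returns to the server, this time in answer to dropout in Phase 3: "researchers will monitor and evaluate every day through the server and conduct self-management measurements once a month". It mentions no reminders.

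For the arms, the Phase 3 text under Study phases and data collection gives the experiment group the app, an e-module and training. For the comparator, "the control group will use the whatsapp group to communicate or consult directly with a health provider", and on materials: "Meanwhile, the control group will only get e-modules". A further sentence, not limited to one arm, reads: "Monitoring by a health provider will be carried out using whatsapp group and when patient come to the PHC for routine check up". Outcome assessment is common to both arms: "self-management scores will be done once a month for three months after the intervention both in the experiment group and in the control group", with HbA1c before the intervention and in the third month.

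The third specific aim is "to determine the effectiveness of the application in self-management and glycemic control of patients with T2DM". Expected results and Dissemination and implementation also speak of the app, the latter as input to BPJS Health.

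**The concern.** The app is described as linking patients, families and nurses. Researchers are not one of the three. Their daily checks and reminders serve data quality and retention, so they are study procedures and not a feature of the product under test. If they operate in one arm only, they are a co-intervention that coincides exactly with treatment.

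A patient who is reminded about entering self-management data may pay more attention to self-management, which is an outcome. No analysis named under Data analysis can remove that. The t-tests, their rank-based alternatives and the multiple regression cannot separate two things that are always present or absent together. The matter has to be settled in the design or in how the intervention is named.

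What is at stake is attribution. Routine PROLANIS use of the app would not obviously come with research staff checking a server each day, yet a favourable result would be reported to BPJS Health as a result of the app.

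**Working it through.** **Step 1. Which arm the follow-up reaches.** The text says only that participants are reminded. Three facts point to the app arm: the monitoring runs through a data server; the paragraph is about operating the app and entering data; and only the experiment group receives the app. No server entry is described for controls. This is a strong inference, not stated text.

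**Step 2. Contacts side by side, on that inference.**

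| Contact | App arm | Control arm |
|---|---|---|
| Researcher checks through the server | daily, three months | none stated |
| Researcher reminders | yes, frequency not stated | none stated |
| E-module | yes | yes |
| Health provider by WhatsApp group | monitoring sentence names no arm | yes |
| Routine check-up at the PHC | yes | yes |
| Monthly self-management measurement | 3 per patient | 3 per patient |

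The first two rows are the asymmetry. The rest is shared or open to both arms, apart from the app itself with its training.

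**Step 3. Planned exposure.** The group size is from the sample-size paragraph: "four participants will be added so the number of samples needed is n1 = n2 = 39 participants".

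- Checks per app patient: 3 months × about 30 days = about 90.
- App arm: 39 × 90 = 3,510 patient-day checks. Control arm: 0 on the inference in Step 1.
- Monthly measurements after baseline: 39 × 3 = 117 in each arm.
- Reminders per app patient: not stated. Assuming at most one per check, the range is 0 to about 90.

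These figures count look-ups. They say nothing about the size of any effect.

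**Step 4. Illustration of what a follow-up effect would do.** First, the plan's own figure. With SD 0.9, difference 0.6, and z values 1.96 and 0.84, n = 2 × (0.9 × 2.80 / 0.6)² = 2 × 4.2² = 35.28, which agrees with the stated 35. An assumed dropout of 10% gives 35 / 0.9 = 38.9, hence 39.

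Now suppose that the app has no effect of its own, that researcher follow-up shifts the outcome by s, and that the groups are otherwise comparable. With 35 per group the standard error is 0.9 × √(2/35) = 0.215. The chance of a significant result is Φ(s/0.215 − 1.96) + Φ(−s/0.215 − 1.96):

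- s = 0: 5%
- s = 0.1: 7.5%
- s = 0.2: 15%
- s = 0.3: 29%

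The values of s are assumptions with no source in the document. They show only that a shift well below the planned 0.6 would matter; they do not suggest that one exists.

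**The case against.** The strongest reply is that the arm, the dose and the effect are all unestablished. Much of it stands.

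- **Arm.** A reader might infer that the protocol states follow-up for app users only. It does not. Strengths and limitation offers server monitoring as an answer to Phase 3 dropout in general, alongside a measurement made in both arms, and the data-collection flow figure is not available here. The inference remains strong because there is no described way for a control patient to appear on the server.
- **Content.** A reader might infer that researchers will prompt self-care. The stated purpose of the reminders is to avoid data-entry errors. An effect on self-management is plausible but indirect, and the protocol does not say that patients must enter data daily; only the monitoring is daily.
- **Completion.** A reader might infer that reminders will make withdrawal differ by arm, because patients lacking self-management results are withdrawn. Those results are the monthly scores, collected in both arms by research assistants. A missed app entry is not shown to trigger withdrawal, so differential completion is not established.
- **Control contact.** Controls have direct access to a health provider. That is real support, but it is not researcher follow-up, and no daily frequency is given for it.
- **Pragmatic package.** Testing an app together with the support around it is legitimate. In that case the package has to be named, and at present the aim and expected conclusions name the app alone.

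Reminder frequency and wording are details that a condensed article may leave to the full protocol, so their absence is not part of this point.

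**Conclusion.** The point holds in a limited form. As written, the plan adds researcher monitoring and reminders that very probably operate in the app arm only, and then attributes the whole between-group difference to the app. The difference may therefore include an effect of researcher follow-up on self-management or HbA1c. The document gives no basis for its size, and the effect could be nil.

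The stronger statement, that the comparison cannot estimate the app's effect at all, is not supported. It would require that reminders are actually sent, that only one arm receives them and that they change the outcomes, and none of these is stated. The 3,510 checks measure planned exposure, not bias.

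The conclusion rests on one inference (the server serves the app, so only app users are followed) and one reading (researchers are outside the intervention, since the app links patients, families and nurses). It is more than a missing detail, because no planned analysis could separate the two components afterwards and the remedy is cheap before Phase 3 starts. It merits a change, at medium confidence.

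**What to change.** Before Phase 3 starts:

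1. State which arm the server monitoring and reminders apply to.
2. Limit researcher contact arising from server checks to technical faults and data-entry errors. This is close to the purpose already given, but should be written as a limit. Any self-care reminder should come from the app, the family or the PROLANIS nurse.
3. Send one identical retention message before each of the three monthly measurements in both arms, through the app or the WhatsApp group.
4. Log researcher contacts by arm and report them with the results.
5. If researcher reminders are kept in the app arm only, describe the intervention, the aim and the conclusion as app plus researcher follow-up, including in the message to BPJS Health.

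The cost is protocol wording, a contact log and three short messages per patient, with no extra patients or tests. A possible downside is slightly more missing app entries.

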### Strengths and limitation

This study offers availability of an integrated diabetes self-management program using Indonesia-language. An android application that involves patients, families and nurses and is useful to guide patients and facilitate monitoring of families and nurses to pay more attention to the implementation of the self-management of patients with diabetes in order to improve their self-management and glycemic control. This android-based IDSM Application can also be used as a means to evaluate the implementation of PROLANIS program at the PHC level, especially among Patients with T2DM.

One limitation in this study is that this research specially in phase 3 will be conducted in three months which might have the potential of participants to drop out before the study is finish. To anticipate this, researchers will monitor and evaluate every day through the server and conduct self-management measurements once a month.

## Dissemination and implementation

This study will provide opportunities for other researchers who need our data by contacting the corresponding author. Dissemination of findings and data sharing will be done after this research is completed. To facilitate data access and data protection during the research process, we will report any research progress to all teams regularly. This study’s results will be published in reputable international journals. The results of this study will be applied in the development of medical surgical nursing, especially in the management of diabetes. The results of this study will also provide input for the government, especially BPJS Health, that this android-based IDSM Application can be used as a means or media in supporting the implementation of self-management of patients with T2DM who are PROLANIS members in Indonesia.

## Conclusion

This study protocol explains the purpose, significance and scope of the mixed methods approach as a comprehensive research design. The findings of this study are expected to help optimize the implementation of diabetes self-management so that it can improve glycemic control of patients with T2DM as one of the indicators of the PROLANIS program at PHCs in Yogyakarta city. The aim of the research team to publish this protocol is to increase the transparency of the study and can provide a reference for other researchers so that the published research protocols can prevent unnecessary duplication.
